#### Study outcomes

To address Aim 2, several clinical outcomes are assessed. *Primary outcome*: proportions in each group achieving or improving risk factor control status (BP < 140/90 mmHg, fasting blood glucose (FPG) < 110 mg/dl, low-density lipoprotein (LDL) < 100 mg/dl, abstinence from smoking/tobacco use: at least 3 out of 4 risk factors). Secondary outcomes: 1) between group difference in number of optimal cardiovascular health indicators (BP < 120/80 mmHg, TC < 200 mg/dl, FPG < 100 mg/dl, >150 min/week of moderate intensity physical activity, BMI < 25 kg/m2, never used tobacco or quit >6 months ago and a healthy diet score) [18], 2) between group mean difference in main risk factors (SBP, DBP, LDL, FPG, and HbA1c), 3) proportions meeting >80% of recommended process measures (smoking cessation, moderate or high intensity physical activity, and <5 g per person/day salt consumption, >3 daily servings of fruits and vegetables, <2 table spoons/cubes of free sugar), and 4) proportions achieving or maintaining ten year Framingham cardiovascular disease (CVD) risk score [19]/WHO CVD risk score [20] of <10% or the INTERHEART non-laboratory based score of <5 [21].

### Study intervention overview

Usual care arm: The usual care arm will be screened for CVD risk factors. Screening results plus one time education regarding management of risk factors will be provided to all family members. Patients with hypertension, diabetes and dyslipidemia in the control arm will be also referred to a primary health care facility. Treatment arm: The study intervention is designed to leverage the existing health care infrastructure available at the community level. Trained FCHW will be visiting the families to promote lifestyle intervention strategies at least once in two months during the intervention phase. The intervention will consist of three phases: 1) screening and detection of CVD risk factors, 2) lifestyle (nutritional/physical activity education and tobacco cessation) counselling 3) FCHW assisted linkage to primary care and 4) active follow-up through a mobile phone application.

#### Intervention Part 1. Screening for CVD risk factors (CONTROL AND TREATMENT ARMS)

All eligible adults in the selected families who provide written informed consent will undergo a screening procedure for CVD risk factors. The families will then be randomized to either the treatment or control arm. At the start of the intervention program, high risk patients in the usual care arm will be referred to the existing primary care system for further management.

#### Intervention Part 2. Lifestyle Education (TREATMENT ARM)

Lifestyle education intervention: The lifestyle education component of the treatment arm will include 9–12 nutritional/tobacco/physical activity consultations. All study participants within the selected families in the treatment arm will participate in the lifestyle education component. Within 30 days of study enrolment, all participants will complete culturally specific semi-quantitative food frequency questionnaires (FFQ) and tobacco use surveys. FCHW will receive training from study staff prior to study implementation. Recommended diet modifications for participants will focus on maintaining a healthy weight via redistribution/reduction of calories (by avoiding fried foods and sugar-sweetened beverages), increasing fiber and protein intake via wheat and sprouted pulses, reducing glycaemic load by switching from refined white rice and bread to whole wheat, increasing fruit and vegetable consumption, and reducing salt and sugar intake. Tobacco cessation and strategies to change sedentary behaviour will also be discussed in the nutritional/tobacco/physical activity consultations. Current tobacco users will complete culturally appropriate cessation action guides that identify triggers and action steps to promote tobacco-free behaviours. Strategies to improve physical activity levels of all members of the family will be discussed at least two times during the intervention phase. Family consultations will be repeated every two months to assess dietary, physical activity and tobacco use changes. FCHW workers will also conduct peer-support group education meetings with groups of 10 participants/families once in two months. Support group meetings will review diet modification and tobacco cessation recommendations and highlight peers’ strategies that have led to successful improvements in diet. All individuals with elevated CVD risk factors will be invited to participate in at least 3 such peer-led support groups during the period of the trial.

Linkage to primary care system: All high risk patients from the treatment arm will be linked to appropriate primary care clinics with assistance from FCHWs. FCHWs will assist high risk patients to identify primary or secondary care facilities and help them schedule initial appointments. For 24 consecutive months following initial screening and randomization, participants from the intervention arm will receive quarterly phone interviews to measure primary care clinic utilization and to assess CVD risk factor management activities (lipid examinations, smoking cessation programs, hypertension control, glucose monitoring).

#### Materials for intervention

We will adapt previously developed strategies in similar studies for development of the intervention materials [17]. Initially, each component of the healthy lifestyle behaviour related to CVD risk reduction (diet, physical activity, tobacco, alcohol and adherence to treatment) will be broken down into performance objectives for the family. Given the practical feasibility of implementation, resource constraints and the local context, these components will be prioritized. In the final step, key potential change objectives and the corresponding intervention options will be set at both the individual and family level. To communicate the selected change objectives clearly and concisely, we will develop different tools after conducting several FGDs with the potential participants and FCHWs. Based on their inputs, materials such as pamphlets for the family, a hanging calendar to describe the dietary priorities for cardiovascular health in the family and an individual diary to set behavioural goals for each month will be developed. These materials will undergo translation into the local language and will be used during FCHW training. They will ultimately serve as communication aids between the FCHW and family members.

#### Care coordination and follow-up

Each family in the treatment arm will be assigned a FCHW. During the intervention phase, FCHW workers will meet with study patients once in two months to assess study progress and participation. In addition, questionnaire data collection and blood draws at home visits after study months 12 and 24 will help to assess detailed attributes of cardiovascular management (FPG, HbA1c, BP, and LDL measures). A mobile phone SMS platform will be used to enhance follow-up. Via SMS, patients will receive study visit reminders and prompts to encourage adherence to treatment and lifestyle goals.

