### Integrated cardiovascular risk reduction intervention (Aim 2)

A randomized controlled trial of families of individuals with a positive history of CHD will be used to address Aim 2 (Fig. 1). *Eligibility criteria*: Eligible families will include those with at least one family member with physician confirmed CHD diagnosed before the age of 55 years. If there are family members who have died from CHD (physician confirmed deaths) before the age of 55 years, such families will also be eligible to participate in the study. The medical records of CHD patients will be used to confirm the diagnosis and the age of the index case. A written informed consent to the study randomization plan from the head of the family will be a mandatory eligibility criterion. All participating family members will be required to provide individual consent to participate. *Family randomization*: Each family will be randomly assigned to participate in either the treatment intervention arm (integrated CVD risk management) or usual care arm (no interventions other than initial screening). Computer generated random numbers generated by an independent member who is not involved in the study will be used for randomization. Randomization of a family will be performed only after collection of complete baseline data. The outcome assessors and the data manager will be blinded from the intervention assignment. The data analysts will be provided with the intervention assignment only after complete database lock. *Participant eligibility criteria*: A minimum of two members from each family will be included even if they reside in separate houses. Potential participants must be more than 18 years of age and either first degree blood relatives or spouses of the index case. Bedridden and terminally ill patients will be excluded from the study. The detailed study flow chart is presented in Fig. 1. *Follow-up period:* All participants will be followed-up for two years after randomization. Study related measurements will be conducted at baseline, one year and two year time-points. The full study flow chart is presented in Fig. 2.

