#### Data collection

A structured questionnaire will be administered by trained staff to collect relevant data at baseline, one year and two year time-points. The questionnaire includes assessments of demographic and socio-economic variables, general health status, diet pattern, physical activity, tobacco, and alcohol consumption. The World Health Organization (WHO) STEPS instrument for chronic risk factor surveillance has been modified and adapted to capture local, contextual information [16]. Dietary data will be collected using a semi-quantitative food frequency questionnaire on food items that are relevant to chronic diseases and adapted from an ongoing cluster randomized trial in India [17]. Additionally, all participants will undergo anthropometric and BP measurements at three time points (baseline, year 1 and year 2). Anthropometric measurements include height (in cm), weight (in kg) and waist circumference (in Inches). BP and pulse rate will be measured using electronic BP monitors (OMRON HEM-7130-L) at all three time-points. Three measurements will be taken at the respective houses of the participants by trained staff, two minutes apart and after allowing the participant to relax for at least five minutes before starting the measurement. Participants will be instructed not to consume any beverages (coffee, tea or soft drinks) and alcohol at least one hour before taking the measurements. They will also be instructed to abstain from smoking. In fasting stage, 5 ml of blood will be collected at three time-points, centrifuged at source for serum and plasma separation, and transported to the study laboratory. They will be stored under −20 °C freezer. The following biochemical analyses will be performed on the collected blood samples: lipid profile (total cholesterol, LDL cholesterol, HDL cholesterol and VLDL cholesterol), fasting plasma glucose, and haemoglobin A1c (Table 2). Abstinence from tobacco at year 1 and year 2 will be validated by assessing urinary cotinine metabolites. Spot urine samples are collected at year 1 and year 2 for this purpose. The study laboratory is accredited by the National Accreditation Board for testing and calibration of Laboratories (NABL), India and also part of international external quality assurance programs (EQAS) such as EQAS of BIO-RAD.

**Table 2 Tab2:** Study measurements

Study parameters	Method/Instrument

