### Trial sample size and power

The sample size estimates accounts for the expected dependency of variables [22]. This family based RCT with 740 families (370 in each arm) of at least two participants each (minimum of 1480 enrolled participants) and no more than 15% loss to follow-up after 2 years will have 90% power to detect an estimated 10% difference in the proportion of participants at 3 or more CHD risk factor goals, the primary effectiveness endpoint of this trial (55% in the intervention group as compared to the expected rate of 45% in the control group). The baseline rate of the composite primary outcome in a large cluster randomized trial in India [17] is used as the expected rate in the control group (data not published) and the lower limit of 95% confidence interval of the improvement in the same composite outcome in a demonstration project in India [13] is used to estimate the rate in the intervention group (data not published). This is for a two sided test with an alpha of 0.05 and a rho or intra-cluster correlation coefficient (ICC) of 0.20. The ICC of the composite primary outcome is also estimated from the baseline data of the above mentioned cluster randomized trial [17]. The power in this study is more than 80% for all secondary endpoints of interest including the change in risk scores.

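### Visit reminders sit inside the treatment-arm SMS package with no stated usual-care equivalent, so effort to retain participants for the outcome visits may differ by arm

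*Protocol article*

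**What the plan says.** Under Care coordination and follow-up, the protocol article starts with the community health worker assigned to each treatment-arm family and that worker's two-monthly meetings. It then mentions "questionnaire data collection and blood draws at home visits after study months 12 and 24", introduces an SMS platform meant to improve follow-up, and states: "Via SMS, patients will receive study visit reminders and prompts to encourage adherence to treatment and lifestyle goals". No arm is named in that sentence.

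Three other places bear on who receives the messages:

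- Study intervention overview lists "active follow-up through a mobile phone application" as the fourth component of the treatment arm.
- The Aim 2 section describes a "usual care arm (no interventions other than initial screening". The overview adds one-time education and referral for that arm.
- The paragraph on linkage to primary care confines the quarterly phone interviews to the intervention arm.

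Outcome collection applies to both arms: "All participants will be followed-up for two years after randomization". Blood pressure is taken at home: "Three measurements will be taken at the respective houses of the participants by trained staff". The sample size allows for "no more than 15% loss to follow-up after 2 years", with no figure by arm.

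**The concern.** A visit reminder serves the conduct of the trial; a prompt to follow treatment or lifestyle goals is part of what is being tested. The article puts both in one sentence, in a paragraph about treatment-arm care. Read in context, the reminders belong to the treatment package and usual care has no described counterpart.

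The outcome is observed only in people who can be found and measured at months 12 and 24. If one arm is prompted for those visits and the other is not, loss may be unequal. If those lost also have worse risk factor control than those who stay, the arm that loses more looks better than it is. With more loss in usual care, the effect would be understated; if those lost were better controlled than average, it would be overstated.

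If the recipients are participants in both arms, the retention problem disappears, but the same sentence then sends intervention content to controls. The sentence needs separating on either reading.

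**Working it through.** **1. Who gets the reminders?**

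| Place in the article | Bearing on the question |
|---|---|
| Care coordination and follow-up, opening | Treatment-arm families and their assigned worker |
| Same section, SMS sentence | Recipients are patients, no arm named; reminders joined to adherence prompts |
| Study intervention overview | Mobile-phone follow-up is a treatment-arm component |
| Aim 2 section | Usual care receives nothing beyond initial screening |
| Linkage to primary care | Quarterly calls in the intervention arm |

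Treatment-arm-only SMS is an inference, but the text points that way.

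**2. The plan's own sample size.** Inputs from Trial sample size and power: 55% against 45%, two-sided alpha 0.05, power 90%, ICC 0.20, two participants per family, 15% loss.

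- Two proportions, pooled variance: [1.960 × √(2 × 0.5 × 0.5) + 1.282 × √(0.45 × 0.55 + 0.55 × 0.45)]² / 0.10² gives 524 per arm.
- Design effect 1 + (2 − 1) × 0.20 = 1.2, so 524 × 1.2 = 628.8, rounded up to 629.
- 629 / (1 − 0.15) = 740 per arm, or 370 families per arm and 1480 participants in all.

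The stated figure reproduces. The effective size after loss is 740 × 0.85 / 1.2 = 524 per arm, with power 90.0%.

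**3. What unequal loss could do (illustration).** The loss splits and the deficit g among those lost are assumptions; only the rates and the 15% average come from the article.

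Let an arm have true rate p and loss d, with those lost at p − g. Then:

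observed rate = [p − d(p − g)] / (1 − d) = p + g × d / (1 − d)

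observed difference = 10 points + g × [d_T / (1 − d_T) − d_C / (1 − d_C)]

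The bracket is 0 for 15%/15%. For 12%/18% it is 0.1364 − 0.2195 = −0.0831. For 10%/20% it is 0.1111 − 0.2500 = −0.1389.

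| Loss, treatment / control | Difference, g = 10 points | Difference, g = 20 points | Power |
|---|---|---|---|
| 15% / 15% | 10.0 | 10.0 | 90% |
| 12% / 18% | 9.2 | 8.3 | 84% to 77% |
| 10% / 20% | 8.6 | 7.2 | 80% to 65% |

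Power uses the observed rates with 740(1 − d)/1.2 effective participants in each arm.

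**4. Which condition does the damage?** Unequal loss alone costs almost nothing: with the difference held at 10 points, power at 10%/20% is 89.9%. With g = 0 the added term vanishes whatever the split. With no true effect (45% in both arms) and 10%/20% loss, the bias is 0 if those lost succeed at 45%, −1.4 points at 35% and −2.8 points at 25%. Both conditions are needed, and the article establishes neither.

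**The case against.** A reader might infer that reminders definitely go to the treatment arm only, that attendance at the outcome visits will therefore differ, and that the comparison will be biased. The documents do not support that, for these reasons:

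- **Recipients.** The sentence names no arm and does not exclude controls. The sentence on month-12 and month-24 data collection, which concerns all participants, comes shortly before it. This stands: the restriction is a reasonable inference and is not stated.
- **Home visits.** Staff go to participants' houses, so the model is not clinic attendance. This is the strongest objection and it weakens the link between a text message and retention. It does not break it: the participant must still be traceable, present, fasting for the blood draw and willing, and the plan allows up to 15% loss despite home collection.
- **Blinding and analysis.** "The outcome assessors and the data manager will be blinded from the intervention assignment". That protects measurement but does not equalise loss. The Data analysis plan includes marginal structural models for loss to follow-up. These help, but they correct only for measured predictors of loss, and no usual-care measurement is described between baseline and month 12.
- **Larger asymmetries.** Two-monthly worker visits and quarterly calls are probably a bigger influence on retention, and they are part of the intervention. This stands. Reminders are the part that can be separated.
- **Condensed article.** How control families are told of visits may be left to the full protocol. Silence there is not itself a fault. The point rests on what the article does say, namely that reminders and intervention prompts travel together.

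**Conclusion.** The point holds as a cheap improvement. As written, retention effort for the month-12 and month-24 home visits may differ by arm, or, on the alternative reading, intervention prompts would reach controls. It is not a demonstrated bias.

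The size is unknown. Under the assumed splits and a deficit of 10 to 20 points among those lost, the planned 10-point difference would be observed as 9.2 to 8.3 points (12%/18%) or 8.6 to 7.2 points (10%/20%). Nothing in the article links the reminders to either split. In these scenarios the error runs against the intervention; it reverses if those lost are better controlled than average or if the treatment arm loses more. The sample size calculation is unaffected and reproduces.

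**What to change.** Split the SMS sentence in Care coordination and follow-up into two:

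1. Reminders of the month-12 and month-24 home visits go to participants in both arms, with identical wording, by the same platform and on the same timetable. They carry appointment information only and no health content.
2. Prompts on adherence and lifestyle goals go to the treatment arm only.

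Report loss to follow-up by arm at both time points, because equal reminders do not remove the asymmetry from worker visits and quarterly calls.

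The cost is a few extra texts per control participant on a platform already planned, and a short amendment. The downside is a minimal extra contact in usual care.

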### Cost effectiveness and acceptability analyses (Aim 3)

The intervention costs will include the resource inputs (e.g., personnel salaries, and materials) that are required to deliver the intervention (in total and per participant). Direct and indirect costs incurred by each family will be estimated using questionnaires administered at study visits 0, 12 and 24. Questionnaires will capture direct medical costs, direct non-medical costs (travel), and indirect costs (missed work time, and lost productivity). To estimate the cost-effectiveness (cost per one count decrease in clustering of risk factors), the between trial group difference in intervention delivery and patient direct costs will be divided by the between group difference in clustering of risk factors or cardiovascular risk score: [costs treatment arm – costs standard arm]/[ΣΔ Primary outcome-Treatment arm] – [ΣΔ Primary outcome-usual care arm]. Similarly, incremental cost utility ratio will also be calculated using data from a 12 monthly health utility assessment. Quality adjusted life years (QALY) will be used as the measure of health utility. The acceptability of the interventions will be assessed through qualitative research. Semi-structured FGDs (4-6 each in men and women) and in-depth interviews with FCHW (6 interviews) will be used to gauge the acceptability of the interventions.

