## Methods

The major aims of the study are as follows: (1) to identify barriers to implementing an integrated cardiovascular risk management program in families of individuals with a positive history of CHD, (2) to assess the effectiveness of an integrated cardiovascular risk management strategy (consisting of screening for risk factors, lifestyle education and linkage to primary care for cardiovascular risk factor management) on modifying risk factor clustering in families, and to assess changes in BP, lipids, glucose, haemoglobin A1c (HbA1c), smoking, diet and physical activity and (3) to estimate the scalability of the integrated cardiovascular risk reduction strategy in families of individuals with a positive history CHD for state- or nation-wide implementation.

The proposed project uses mixed methods to achieve the study aims. The three design approaches include: Aim 1, formative qualitative research; Aim 2, a randomized controlled trial; and Aim 3, cost effectiveness and evaluative qualitative research to inform acceptability and scalability.

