To compare the cost-utility of the intervention to standard arm management, we propose to calculate an incremental cost/utility ratio [net costs to net utility: costs of intervention – costs of control/utility of intervention – utility of control]. To calculate utility, we will use 12-monthly health utility. The chosen measure of utility will be the closest option to a global measure, the quality adjusted life year (QALY], and is calculated as the sum of mean survival time [life years] x utility scores at 12 and 24 months [25]. Both 12 and 24-month costs per QALY will be reported. If the intervention is successful, the modeled long-term cost-utility of the intervention and usual care will be compared using Markov Chain Monte Carlo estimation techniques, controlling for age, gender, and risk factor prevalence under different plausible scenarios for how these may evolve over time [26]. Then it will be compared to reference points from the literature – e.g., ceiling ratios for costs per QALY that are less than three times gross domestic product (GDP) per capita [27, 28] that are considered cost-effective [29] (India’s 2013 GDP per capita was $3990; threshold: ≤$11,100 per QALY).

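### Provider-funded primary care generated by linkage is not costed, so the scale-up ratios are likely to understate incremental cost to the extent that families do not pay for it

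*Protocol article*

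**What the plan says.** The section Cost effectiveness and acceptability analyses (Aim 3) describes two kinds of cost. The first is programme cost: "The intervention costs will include the resource inputs (e.g., personnel salaries, and materials) that are required to deliver the intervention". The second lies on the participants' side: "Direct and indirect costs incurred by each family will be estimated using questionnaires" at visits 0, 12 and 24, covering medical spending, travel and lost work. For the cost-effectiveness ratio, "the between trial group difference in intervention delivery and patient direct costs will be divided by" the difference between arms in risk-factor clustering or risk score.

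The same section then introduces the cost-utility ratio with the word *Similarly*. The Data analysis plan writes that ratio as "costs of intervention – costs of control/utility of intervention – utility of control" and lists no cost categories. It goes on to a modelled long-term comparison and sets the result against a ceiling of $11,100 per QALY.

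On care received, the linkage paragraph under Intervention Part 2 says "All high risk patients from the treatment arm will be linked to appropriate primary care clinics with assistance from FCHWs", with help in making first appointments. In the other arm, according to Intervention Part 1, "high risk patients in the usual care arm will be referred to the existing primary care system for further management". The linkage paragraph also plans quarterly telephone interviews over 24 months on clinic use and risk-factor management, for the intervention arm only. The aims listed under Methods give the purpose of Aim 3 as judging scalability "for state- or nation-wide implementation".

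**The concern.** The intervention works partly by moving people into a health service that already exists and that somebody has to fund. Any extra consultations, laboratory tests and medicines are an intended result of the linkage component. The part that families do not pay for falls outside both cost headings: clinics do not spend it on delivering the programme, and households do not incur it.

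Its benefit is not left out in the same way. Better control of blood pressure, glucose and LDL feeds the outcome in the denominator, however the treatment was paid for. The ratio can therefore credit the effect of provider-funded care without charging for it, and a programme that leans more on that care has more cost outside the calculation. What primary care would have to fund is central to a decision on state or national roll-out, and that is the decision Aim 3 is meant to inform.

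**Working it through.** The article gives no unit costs, no expected primary-care use and no expected ratio, so there is no economic figure of its own to reproduce. The check has two parts: what the stated numerator contains, and how an omitted term would move the ratio.

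**Part 1. Which costs are counted**

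| Cost item | Where it would enter | Counted as written? |
|---|---|---|
| Programme staff and materials | delivery inputs (Aim 3 section) | yes |
| Visits, tests and medicines paid by the family | family direct medical cost (Aim 3 section) | yes |
| Family travel | family direct non-medical cost (Aim 3 section) | yes |
| Visits, tests and medicines paid by the clinic or health system | neither of the two numerator terms | no |
| Primary-care use in the intervention arm | quarterly telephone interviews (linkage paragraph) | measured, but not tied to costing |
| Primary-care use in the control arm | no measure described | not measured |

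The last two rows matter for repair. An incremental provider cost needs use in both arms. The telephone interviews cannot supply it, whatever unit costs are added later.

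**Part 2. Effect on the ratio**

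Let C be the incremental cost that is counted (delivery plus patient direct costs), H the incremental provider cost that is not counted, and E the incremental effect, with C and E both positive.

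- Reported ratio = C / E
- Full ratio = (C + H) / E
- Full ÷ reported = 1 + H/C
- Understatement as a share of the full ratio = H / (C + H)
- Reported ratio at which the full ratio reaches the ceiling = 11,100 / (1 + H/C)

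H/C cannot be taken from the documents. The values below are assumptions chosen to show the range.

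| Assumed H/C | Full ÷ reported | Understated by | Reported ratio at which the full ratio equals $11,100 |
|---|---|---|---|
| −0.10 | 0.90 | −11.1% (overstated) | $12,333 |
| 0 | 1.00 | 0% | $11,100 |
| 0.10 | 1.10 | 0.1/1.1 = 9.1% | $10,091 |
| 0.25 | 1.25 | 0.25/1.25 = 20.0% | $8,880 |
| 0.50 | 1.50 | 0.5/1.5 = 33.3% | $7,400 |
| 1.00 | 2.00 | 1/2 = 50.0% | $5,550 |

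The first row is there because H is a difference between arms and can be negative, for instance if provider savings outweigh the extra contacts. The last column applies only if the cost-utility ratio uses the same two cost terms. It takes the ceiling as printed. (Three times the printed GDP figure is 3 × $3,990 = $11,970, which is a separate matter.)

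**The case against.** **Who pays is not stated.** This is the strongest objection, and it stands. The documents do not say that the linked clinics are free at the point of use, and the linkage paragraph allows for secondary as well as primary facilities. Care paid in full by the family is already captured as direct medical cost. A reader might infer that the ratio definitely understates cost, or that the gap is all public money; the documents support neither.

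**The control arm also receives care.** This stands too. High-risk control participants are referred after screening and one-time education, so only use beyond theirs counts. The contrast is assisted linkage against plain referral. More use in the treatment arm is the aim of that contrast, but its size is unknown.

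**The ceiling belongs to a different ratio.** The two-term numerator is written for the cost-effectiveness ratio. The $11,100 ceiling belongs to the cost-utility ratio, whose cost categories are only implied by *Similarly*, and it follows a modelled comparison whose cost inputs are not described. That weakens the link to the ceiling. It leaves the cost-effectiveness numerator as stated.

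**A fuller document may settle it.** The list of delivery inputs is open-ended, and perspective and unit costs are often left to an economic analysis plan. But the open list covers only what is needed to deliver the intervention, and the numerator sentence names two terms. Even if clinic care were read into delivery, no control-arm use is described from which to form a difference.

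**Averted events could offset the cost.** They could, but the Discussion says that the two-year study is not powered for cardiovascular morbidity and mortality, so within-trial savings cannot be relied on.

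**A visit count is tempting but unsound.** A reader might take 1 − 0.45 = 55% of participants as needing care, assume up to 4 extra visits a year for two years, divide by the planned 10-point effect, and reach 0.55 × 4 × 2 / 0.10 = 44 uncosted visits per extra participant at goal. (With 30% and 1 visit a year the result is 6.) Missing three of four risk-factor goals is not the same as needing primary care, the visit rates have no source in the documents, and neither planned ratio is expressed per extra participant at goal.

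**Conclusion.** The point holds in conditional form. As written, the cost-effectiveness numerator leaves out primary care that linkage generates and families do not pay for, and the cost-utility ratio appears to inherit the omission. The ratios are likely to understate incremental cost if two conditions are met: linkage raises use above that of the referred control arm, and part of that use is not paid by families. The first is the purpose of the component; the second is not stated anywhere.

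The size cannot be computed. The 9% to 50% range holds only for an assumed provider cost of 10% to 100% of the counted incremental cost. The point concerns the economic aim alone and does not touch the primary effectiveness analysis. It merits correction because the omission is one-sided by construction, it bears on the scale-up conclusion, and the planned collection of use data could not repair it afterwards.

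**What to change.** 1. State the costing perspective and make it include the health system.
2. Record primary-care contacts, tests and medicines with the same items in both arms, through the existing cost questionnaire at 12 and 24 months. Do not use the intervention-arm telephone interviews for the between-arm difference.
3. Value this use at provider unit costs from a list fixed in advance, net of what families paid, so that nothing is counted twice.
4. Define incremental cost as delivery plus health-system plus family costs, and use that definition in the within-trial cost-effectiveness and cost-utility ratios and in the long-term model.

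The cost is a few questionnaire items and a unit-cost list. The added items rely on recall over 12 months, which will introduce error. The resulting ratio will probably be less favourable to the intervention.
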